#### Intervention Description

A total of sixteen 60-minute DfPD classes will be conducted twice weekly for 8 weeks, both in-person and online, in a physiotherapy facility in Athens, Greece (in-person DfPD), and via Zoom platform (online DfPD; Zoom Communications, Inc), which will be free for the participants; the facility is licensed for the establishment and operation of physiotherapy activities. All the dance classes will be instructed by the main investigator (ME), who holds the approval to use DfPD for research reasons and is a licensed neurological physiotherapist, adapted physical educator, and dance educator. The exact structure and content of the program are described in Table 4. Participants will be instructed individually on how to use the Zoom platform before their program entry. Frequency and duration of the program are in accordance with past exercise and dance programs in patients with PD [30,45-48].

**Table 4 table4:** UPGRADE-PD (Upbeating Greek Application of Dance in Parkinson’s Disease) study’s DfPD structure and content.

Part (category) and track number		Type of activity		Type of exercise	Primal goals	Song title, album title (release date), composer

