**1 (seated warm-up)**						
	1	Introduction: “The Sun Salutation”	Breathing exercises and gradual early mobilization		General warm-up, increase of concentration, and general mobilization	“Love in the Heart” (remastered 2004), *30 Nocturnes* (1987), Manos Hadjidakis
	2	Introduction to flow: legato	Gradual moderate intensity and limp and torso mobilization		Specific warm-up and introduction to contemporary dance	“By the Sea,” *Eternity and a Day* (1998), Eleni Karaindrou
	3	Storytelling: “The Outside the Window Travel”	Introduction to spine twist movements and arm waves		Aesthetics, fantasy stimulation, and visualization	“The Young Rallou” (remastered 2004), *30 Nocturnes* (1987), Manos Hadjidakis
	4	Introduction to upper limb velocity: staccato	Tapping movements, rotational arm movements, gestures, and visual contact		Coordination, diadochokinesia, and group dynamics	“The River,” *The River* (1959), Manos Hadjidakis
	5	Story telling: “The Ocean Dive”	Torso and upper extremities “waving”		Fantasy and imagination stimulation and visualization, successive movement	“Two,” *Two* (2006), Konstantinos Vita
	6	Limb and torso mobilization	“Flex point”		Coordination and seated posture	“Who Pays the Ferryman,” *Who Pays the Ferryman* (1977), Yannis Markopoulos
	7	Storytelling: “High Five”	Arm waves, stretch side to side, high five in pairs interaction, and spine rotation		Social interaction, spine mobilization, and group dynamics	“When the Clouds Come,” *Gioconda’s Smile* (1965), Manos Hadjidakis
	8	Introduction to velocity: staccato	Rhythmical walking on the spot and transition of weight		Rhythm, speed switching, and coordination	“Rain,” *Gioconda’s Smile* (1965), Manos Hadjidakis
	9	Storytelling: “Opa”	Staccato-and-legato body movements		Social interaction, speed switching, and movement dynamics (staccato-legato transitions)	“I Hartaetoi” (remastered), *I Gitonia Ton Aggelon* (2004), Mikis Theodorakis

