
#### Culturally Tailored Therapeutic Dance Intervention

Most nation states were created during the 19th century, when cultural elements were used as potent symbols to serve each national identity [69], such as music and dance [70]. Dance has been used as a powerful tool in the creation of national identity [71] and as a national symbol that seems to emotionally empower members of a community [72]. Particularly in Greece, events involving dance are used for entertainment, socializing, and escape from everyday routine, as well as a sign of well-being that underpins the Greek national identity [73,74].

Dance is a physical activity in which the basic tool is the human body and its purposefully selected movements in a potentially varied rhythmical and cultural context [8]. Dance can be defined as ethnic, where movement types and motivation agree with the way of life and socially accepted norms of a period, and theatrical, where movement patterns are consciously designed to be shown to an audience that is not necessarily familiar with its context [75], even considering that every dance in any context contains ethnic elements [76]. Each person, even unconsciously, dances, bringing to bear all their past intra- and interpersonal experiences and cultural values within the specific socioeconomical environment they live [77], we decided to examine the effect of our dance intervention practice taking into consideration the cultural background of the targeted individuals, who in our case were Greek patients with PD.

DfPD is a dance intervention specially designed for patients with PD, which integrates different dance genres, encourages dance exploration, and focuses on dancing individually and in groups rather than in pairs [45]. For culturally adjusting this intervention to our population, we proceeded with several actions, as noted subsequently. First, we adopted the term “culturally tailored,” instead of “culturally adjusted,” as it has been already proposed in past research and it refers to the total sum of adaptations that must be done in terms of content, symbolisms, and strategies in an intervention to best suit specific cultural characteristics, and thus positively affect health behavior and cultural expression [78].

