### Recruitment

Recruitment started 6 months before the starting date of the program via relevant printed information material and health care practitioners (neurologists and nurses) of the Eginition University Hospital Neurological Outpatient Clinic. All study procedures have been discussed face-to-face individually with each potential participant before screening for eligibility by the primary researcher. The primary researcher (ME) has obtained written informed consent from the potential clinical trial participants before the study’s inclusion.

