### Data Collection and Management

All assessments will be conducted face-to-face by an independent investigator to eliminate possible detection bias, except of the Movement Disorder Society-Unified Parkinson’s Disease Rating Scale and Montreal Cognitive Assessment, which will be conducted face-to-face by specialized neurologists of the Eginition University Hospital Neurological Outpatient Clinic.

Participants are free to quit at any time if they wish to discontinue the study. In that case, reasons for withdrawal will be recorded, if this is possible. Participant’s enrollment will be followed by the research team’s assistance during the entire study period, including scheduling of data collection appointments, reminding of intervention’s appointments, and communicating the starting time of each research period.

Data, including consent forms, completed paper-based data files, and study notes, will be securely stored in the main investigator’s office, which will be locked. Raw data will be encrypted and stored digitally on a local computer with access rights to the main investigator. All original data will be archived for 5 years after the completion of the research and then destroyed, according to local regulations. All written data will be stored in a locked cabinet of the main investigator’s locked office for 5 years and then destroyed. Digital data will be stored on a password-protected local computer.

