### Statistical Analysis

The primary analysis will evaluate the between group differences in total score of the Greek version of Parkinson’s Disease Questionnaire-8 after each research period. Mean (SD) or summary statistics appropriate to the distribution of the QoL total score will be reported by study group (in-person DfPD vs online DfPD vs control). Study groups will be compared in terms of QoL using mixed model repeated measures considering the correlated data from the same patient [128]. Mixed model repeated measures are robust in small sample size studies; thus, a decreased risk of type II errors occurs [129]. For all secondary end points, summary statistics will be tabulated by study group, and study groups will be compared with a statistical method appropriate to the type of the end point (eg, continuous and categorical end point). Bonferroni correction will be used to account for multiple comparisons of secondary outcomes.

A secondary analysis of the primary end point will adjust for those prerandomization variables which might reasonably be expected to be predictive of favorable QoL total score. Any deviations from the protocol will be recorded and agreed by the investigators. Missing data will not be imputed neither for primary nor secondary analyses, and no interim analyses will be conducted in this study. All the *P* values are 2-sided at an α level of .05. Analyses will be conducted with SPSS (version 20.0; IBM Corp) and R (version 4.4.1; R Foundation for Statistical Computing).

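### The primary PDQ-8 model provides only for within-patient correlation, so if patients sharing a dance class are also correlated, its intervals will be too narrow, most of all for in-person versus online

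*Protocol article*

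**What the plan says.** The Statistical Analysis section sets the comparison: "The primary analysis will evaluate the between group differences in total score of the Greek version of Parkinson’s Disease Questionnaire-8". The model is fitted "using mixed model repeated measures considering the correlated data from the same patient". That is the only dependence it names. The Sample Size section likewise uses a single correlation, 0.64 between repeated measurements on one participant.

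Allocation is by individual participant to one of six sequences (Assignment of Interventions: Allocation). Delivery is in classes: "A total of sixteen 60-minute DfPD classes will be conducted twice weekly for 8 weeks, both in-person and online". The section on cultural tailoring says that the program "focuses on dancing individually and in groups rather than in pairs". Interaction is planned content. One seated track in Table 4 has the goals "Social interaction, spine mobilization, and group dynamics" and includes a high five in pairs, and the closing track moves in a circle. Control is usual care without classes (Table 1).

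On the other side of the ledger, "All the dance classes will be instructed by the main investigator", to one fixed 14-track program. The article does not state how many classes run in parallel, their size, or any expected class-level correlation.

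**The concern.** Patients who share a class in a given period share its peers and its interaction, which the program treats as part of the treatment. Their scores after that period may move together. A model with a patient effect alone treats them as independent, so one class that happens to gel, or not to, can be read as an effect of dance or of its format.

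The crossover makes this sharper than the usual design-effect rule suggests. Each patient serves as their own control, so the large between-patient variance drops out of every contrast. A class effect belongs to one format in one period and does not drop out. In-person versus online carries it on both sides, and the Introduction presents that comparison as not previously tested in a randomized trial.

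**Working it through.** **The plan's own figure.** No stated figure covers class correlation. The sample size of 18 (21 after dropout) cannot be rebuilt from the stated inputs alone, because the effect size is not given. With 3 groups, 6 measurements, correlation 0.64, 80% power and an assumed f of 0.25, the repeated-measures interaction test needs 18. The dropout step gives 18 × 1.15 = 20.7 or 18 / 0.85 = 21.2. Nothing in it allows for classes.

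**How many class groups?** 40 patients over three conditions gives 40 / 3 ≈ 13 per condition in each period. Three points suggest one cohort:
- Recruitment: "Recruitment started 6 months before the starting date of the program". First enrolment in April 2023, that lead and a 45-week schedule fit the stated end in September 2024.
- The music list was compiled from the preferences of all participants.
- Table 6 has a denominator of 40 (24 is 60%).

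On that reading each format has about 3 class groups in the whole trial, or 6 if each is split in two. This is an inference.

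**Set-up.** Total variance is 1, patient variance 0.64 and within-patient variance 0.36. The class ICC ρ is a share of total variance, applies to the dance conditions only, and is taken out of the 0.36. There are 40 patients, no dropout and no true effect. The response is the score after each period. The fitted model has patient, period and treatment terms and no class term. Let g be the total number of class groups per format (3 or 6).

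- Nominal variance of any contrast: 2 × 0.36 / 40 = 0.018, SE 0.134.
- True variance, dance versus control: (0.36 − ρ)/40 + 0.36/40 + ρ/g.
- True variance, in-person versus online: 2(0.36 − ρ)/40 + 2ρ/g.

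**At ρ = 0.05, g = 3:**
- Dance versus control: 0.00775 + 0.009 + 0.01667 = 0.0334, SE 0.183, ratio 0.183 / 0.134 = 1.36.
- In-person versus online: 0.0155 + 0.0333 = 0.0488, SE 0.221, ratio 0.221 / 0.134 = 1.65.

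The ordinary design effect, 1 + (13.33 − 1) × 0.05 = 1.62, would give a ratio of only 1.27.

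**At ρ = 0.01, g = 3:**
- Dance versus control: 0.00875 + 0.009 + 0.00333 = 0.0211, SE 0.145, ratio 1.08.
- In-person versus online: 0.0175 + 0.00667 = 0.0242, SE 0.155, ratio 1.16.

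**Simulated rejection rates of a nominal 5% test** (4,000 trials per setting):

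| Class ICC | Classes per format per period | In-person vs control | In-person vs online |
|---|---|---|---|
| 0 | 1 | 5.1% | 5.0% |
| 0.01 | 1 | 7.4% | 9.2% |
| 0.05 | 1 | 15.4% | 24.1% |
| 0.10 | 1 | 25.5% | 37.3% |
| 0.05 | 2 | 10.2% | 14.2% |

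A second, independently written simulation gave 95% interval coverage as follows, first for in-person versus control and then for in-person versus online:
- ICC 0.01, one class: 93% and 90%.
- ICC 0.05, one class: 83% and 77%.
- ICC 0.05, two classes: 90% and 84%.

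The two sets agree to within about 2 percentage points.

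**The case against.** The strongest reply is that nothing in the article shows that class correlation exists. At ICC 0 the planned intervals are right. One instructor and one fixed program remove between-instructor variance, and stable differences between peers go into the patient effect. What remains is deviation specific to one format in one period. The ICC scale also matters: 0.05 of total variance is 0.05 / 0.36 = 14% of within-patient variance, and 0.10 is 28%, which is a strong assumption under one teacher and one script. All of this stands. It is why the point is conditional and why the low end of the range deserves weight.

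A second reply is that the model sentence is condensed. It does not exclude other terms, and random effects may be set out in an analysis plan not shown. That is fair. Still, the article does state which correlation the model handles, and it is not the one that the delivery adds.

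A reader might go further in three ways that the document does not support:
- That the primary intervals are too narrow as a matter of fact. This needs a positive ICC, which is not given.
- That season is a class-level cause. In a single cohort all three conditions share the season within a period, so a period term absorbs it.
- That a particular amount of power is lost. The article states no PDQ-8 effect size, so any such figure rests on an effect chosen by the reader. The 40 randomized also exceed the planned minimum of 21.

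**Conclusion.** The concern holds conditionally. As described, the primary model makes no provision for correlation among patients in the same class group and period. If that correlation is positive, intervals are too narrow and the false-positive rate exceeds .05.

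Under one class per format per period, even ICC 0.01 takes in-person versus online to about 9%, and ICC 0.05 takes it to about 24%. In-person versus control goes to about 7% and 15%. Two classes per format and period at ICC 0.05 give about 10% (in-person versus control) and 14% (in-person versus online).

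These sizes rest on an assumed ICC, an inferred single cohort, the plan's 0.64, no dropout, and the score after each period as the response, as the Statistical Analysis section has it. Change from each period's own baseline, which is how Primary Outcomes words it, would carry more within-patient noise. The relative inflation would then be smaller, in the same direction.

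**What to change.** - Record each participant's class group in each period. The attendance data already needed for adherence supply it. Report the number and size of classes.
- Report the primary contrasts with a class-group variance component in the dance conditions only, control observations standing alone, held at fixed ICCs (for example 0, 0.01 and 0.05), beside the patient-only model.
- Estimate that component freely, with Satterthwaite or Kenward-Roger degrees of freedom, only if enough separate classes were run. With one class per format per period it would rest on six cells, too few to carry the primary analysis alone.
- Limit the in-person versus online conclusion to what survives the plausible ICCs.

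The cost is one identifier and a little more analysis in R, which is already planned, with no new patients or visits. The downside is wider intervals: with one class per format per period, about 8% (dance versus control) and 16% (in-person versus online) wider at ICC 0.01, and about 36% and 65% wider at ICC 0.05, from the SE ratios above.

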### Objective

The primary aim of this study is to investigate the possible effectiveness of a patient-centered and culturally tailored dance intervention delivered both in-person (in-person DfPD) and remotely (online DfPD) on QoL of Greek patients with early- to midstage PD. The key secondary aim is to investigate the safety and feasibility of the aforementioned interventions (ie, in-person DfPD and online DfPD) and its possible effectiveness on fatigue, depressive symptoms, stress, anxiety, sarcopenia, frailty, balance, cognitive functions, movement and nonmovement PD symptoms, and BMI of Greek patients with early- to midstage PD.

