## Methods

### Study Design

This is a single-centered 3-arm crossover and open-label randomized controlled trial (in-person DfPD vs online DfPD vs control) of UPGRADE-PD (Upbeating Greek Application of Dance in Parkinson’s Disease). Blinding among participants and researchers is not possible due to the nature of the study. There are 6 possible research sequences, as shown in Table 1, and 3 possible carryover effects (1, 2, and 3) for each period from the prior intervention, as shown in Table 2. The study will last 10 months for each participant, including three 2-month research periods and two 2-month washout periods. Assessments will be conducted at enrollment (T_−0_=week −1), baseline periods (T_0_=week 0, T_2_=week 18, and T_4_=week 36), and postinterventional periods (T_1_=week 9, T_3_=week 27, and T_5_=week 45), as shown in Table 3. Allocation to each of the 6 possible sequences will occur after the completion of the first baseline assessment, as shown in the participant flow in Figure 1.

**Table 1 table1:** The UPGRADE-PD (Upbeating Greek Application of Dance in Parkinson’s Disease) study design.

Sequence	Period		
	First	Second	Third
ABC	A^a^	B^b^	C^c^
BCA	B	C	A
CAB	C	A	B
ACB	A	C	B
BAC	B	A	C
CBA	C	B	A

^a^Intervention A (in-person Dance for Parkinson’s Disease combined with usual medical care).

^b^Intervention B (online Dance for Parkinson’s Disease combined with usual medical care).

^c^Control group (usual medical care without Dance for Parkinson’s Disease).

**Table 2 table2:** The UPGRADE-PD (Upbeating Greek Application of Dance in Parkinson’s Disease) study’s code for the possible carryover effect.

Sequence	First period		Second period		Third period	
	Trial	Carryover effect	Trial	Carryover effect	Trial	Carryover effect
ABC	A^a^	0^b^	B^c^	1^d^	C^e^	2^f^
BCA	B	0	C	2	A	3^g^
CAB	C	0	A	3	B	1
ACB	A	0	C	1	B	3
BAC	B	0	A	2	C	1
CBA	C	0	B	3	A	2

^a^Intervention A (in-person Dance for Parkinson’s Disease combined with usual medical care).

^b^Noneffect.

^c^Intervention B (online Dance for Parkinson’s Disease combined with usual medical care).

^d^Effect from intervention A.

^e^Control group (usual medical care without Dance for Parkinson’s Disease).

^f^Effect from intervention B.

^g^Effect from the control group.

**Table 3 table3:** The UPGRADE-PD (Upbeating Greek Application of Dance in Parkinson’s Disease) schedule of enrollment, interventions, and assessments for participants.

Time point (wk)		Study period									

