#### Secondary Outcomes

The other expected secondary outcomes are outlined in Textbox 4.

Other secondary outcomes.

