### Conclusions

The results of this study are expected to show the possible differential effect of a patient-centered and culturally tailored DfPD intervention, delivered in-person versus online, on several movement and nonmovement symptoms, as well as on QoL, sarcopenia, and frailty in people living with PD in Greece.

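### Bonferroni for the secondary outcomes has no fixed family; Holm or an omnibus-gated rule would hold 5% over outcomes and contrasts with more power

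*Protocol article*

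**What the plan says.** The Statistical Analysis section of the protocol article gives one multiplicity rule for the secondary end points: "Bonferroni correction will be used to account for multiple comparisons of secondary outcomes". The tests themselves are described only in general terms: "study groups will be compared with a statistical method appropriate to the type of the end point". P "values are 2-sided at an α level of .05". No divisor, list of tests or set of contrasts is given.

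The Objective names the domains: "effectiveness on fatigue, depressive symptoms, stress, anxiety, sarcopenia, frailty, balance, cognitive functions, movement and nonmovement PD symptoms, and BMI". Textbox 4 turns them into scores. Study Setting asks whether each form of dance class improves the clinical parameters against usual care. Principal Findings in the Discussion adds the difference between in-person and remote delivery on every one of these domains. The Conclusions expect results "on several movement and nonmovement symptoms, as well as on QoL, sarcopenia, and frailty in people living with PD in Greece".

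**The concern.** The secondary family has two dimensions: several scores, and three treatments compared on each. A Bonferroni correction controls error only over the tests that its divisor counts. If it counts outcomes, the three contrasts within an outcome go uncorrected. If it counts contrasts within an outcome, the outcomes go uncorrected. If it counts everything, error is held but power is given away.

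The choice decides claims. With 15 scores the per-test thresholds are .05/3 = .0167, .05/15 = .0033 and .05/45 = .0011. A contrast with P=.01 is positive on the first and negative on the other two. A contrast with P=.002 is positive on the first two and negative on the third. The planned statements on symptoms, sarcopenia and frailty all come from this family.

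**Working it through.** **1. Count of tests.** Table 3 lists 10 secondary efficacy instruments: PFS-16, MFIS, DASS-21, SARC-F, EWGSOP2, frailty phenotype, BBS, MoCA, MDS-UPDRS and BMI. Textbox 4 uses DASS-21 as three subscales: 10 + 2 = 12 scores. If the four MDS-UPDRS parts are tested separately: 12 + 3 = 15. Three treatments give 3 pairwise contrasts, so 36 or 45 tests. The plan states no figure of its own to reproduce here.

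**2. Upper reference, all tests independent (m = 15).**
- Divisor 15, 45 tests: 1 − (1 − .05/15)^45 = 14.0%.
- Divisor 45, 45 tests: 1 − (1 − .05/45)^45 = 4.9%.
- One overall test per outcome at .05/15: 1 − (1 − .05/15)^15 = 4.9%.

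**3. Allowing for correlation.** Contrasts within an outcome share treatment means, and outcomes are correlated. The documents give no between-outcome correlation, so a range is assumed. Simulated family-wise error with no treatment effect, m = 15, all scores treated as continuous (ranges are normal and t reference distributions):

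| Rule | corr. 0 | 0.5 | 0.8 |
|---|---|---|---|
| Each contrast at .05/15 | 12.8–13.1% | 9.7–9.9% | 5.4–6.1% |
| Each contrast at .05/3 | 49% | 34% | 19–21% |
| Each contrast at .05/45 | 4.6–4.8% | 3.7–3.9% | 2.2–2.4% |
| Overall test at .05/15, then contrasts at .05/15 | 4.8–5.0% | 3.9–4.1% | 2.2–2.5% |

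With 12 outcomes the first row runs from 13.1% to about 6%.

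**4. Why the gate is valid.** With three treatments, any two true pairwise nulls imply the third, so within an outcome either one pairwise null is true or all three are. If all three are true, a false claim needs the overall test to fail at .05/m. If one is true, only that contrast can err, at .05/m. The error per outcome is at most .05/m, and over m outcomes at most m × .05/m = .05.

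**5. Power against Bonferroni over all tests.** Effect sizes are assumed, since the plan gives none for these scores. Average power for true dance-versus-control contrasts, 10 of 15 outcomes affected, correlation 0.5; n = 40 is the number randomized and n = 34 is 40 × 0.85, using the Sample Size section's 15% dropout:

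| Pattern (standardised paired difference) | n | Bonferroni/45 | Holm/45 | Gate |
|---|---|---|---|---|
| Both dance arms 0.5 | 34 | 32% | 34% | 39% |
| Both dance arms 0.5 | 40 | 41% | 44% | 50% |
| One arm 0.5, the other 0.25 | 34 | 18% | 18% | 19% |
| One arm 0.5, the other 0.25 | 40 | 23% | 24% | 25% |

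For single contrasts at n = 40, in within-subject SD units: with both dance arms at 0.8, Bonferroni 0.576 against gate 0.669. With arms at 0.8 and 0.4, the largest contrast is 0.576 against 0.579 and the smaller ones about 0.062 against 0.113.

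**6. A limit of the gate.** If the third mean lies exactly midway, F = t²/2. At n = 40 the error df are 2 × 39 = 78. The .05/45 threshold is t = 3.39, so F = 3.39²/2 = 5.7, below the overall critical value of 6.14 at .05/15. A contrast with t between 3.39 and √(2 × 6.14) = 3.50 would then pass Bonferroni/45 and fail the gate. Holm has no such case.

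**The case against.** The strongest reply is that the sentence does not commit the sponsor to a faulty count. Multiple comparisons of secondary outcomes can mean every test performed. Equally, the plan never says that three pairwise tests will be run on each secondary score, and one overall three-group test per outcome with Bonferroni over outcomes also fits the words. Both hold 5%. This stands. A reader might infer that the plan as written runs at 9–13% family-wise error; the documents do not support that, because the figure belongs to one reading the text does not fix, and it shrinks to about 6% if outcomes are strongly correlated.

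A second reply is that the divisor and test list belong in an analysis plan, which is not shown. This also stands: their absence from an article is not a finding.

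A third is that Bonferroni over all tests is valid, so preferring something else is taste. In part. It is not an error, and the gate's gain nearly vanishes for the largest contrast when means are evenly spaced. But Holm makes every claim Bonferroni makes, at the same error level and no cost in patients or data. The valid single-test-per-outcome reading, for its part, cannot say which form of delivery works or whether the two differ, which the aims ask.

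The count of 15 depends on splitting MDS-UPDRS, which Textbox 4 describes in parts without saying each is tested. The simulations treat every score as continuous, although sarcopenia and frailty status are categories; the error-control argument carries over to any valid test, the power figures may not.

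**Conclusion.** The point holds as an improvement to a named method, not as an error under every reading. Depending on how the sentence is applied, family-wise error over the secondary outcomes lies at or below 5% (all tests, or one overall test per outcome), at about 13% to 6% (divisor 15), or at about 49% to 19% (divisor 3). The ranges rest on 15 scores, three contrasts each and assumed correlations of 0 to 0.8. Among rules that hold 5% and still answer the pairwise questions, plain Bonferroni is the weakest choice: Holm is never less powerful and gained about 1 to 3 points, and the gate gained about 1 to 9 points on average or for contrasts with appreciable power, though not in every single configuration.

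The primary PDQ-8 analysis is not touched. One might also infer that the outcome tiers leave the family undefined, since the Objective counts fatigue, frailty and the rest within the key secondary aim, while the Secondary Outcomes section says "The other expected secondary outcomes are outlined in Textbox 4". That is a labelling mismatch only: the Statistical Analysis section treats all secondary end points alike and ties no alpha to a tier.

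**What to change.** Replace the Bonferroni sentence, before the data are analysed, with one of these:

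- **Holm.** List the secondary efficacy scores (12, or 15 with the MDS-UPDRS parts separate) and the three pairwise treatment contrasts, and apply Holm's procedure to the full list of 36 or 45 P values at a two-sided family-wise level of .05.
- **Gate.** For each of the m scores, test the 2-df overall treatment effect at .05/m. Only if it is significant, test the three pairwise contrasts, each at .05/m.

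Either statement settles the family, the contrasts and the thresholds together. Safety, feasibility and satisfaction can be declared descriptive and outside the family, and the tier wording in the Objective aligned with the outcome sections.

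The cost is wording only, with no new data or participants. Under the gate, a contrast cannot be claimed when the overall test for its outcome fails. Under both rules the thresholds are stricter than a correction within each outcome alone.
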